| Facility assessment      | X                                     |                   |                |                                                 |                                 |
| Register data extraction | X                                     |                   | X              |                                                 |                                 |
| Health worker interview  | X                                     |                   | X              |                                                 |                                 |
| Patient interview        | X                                     |                   |                | X                                               | X                               |
| Delivery observation     |                                       |                   | X              |                                                 |                                 |
| Process evaluation*      |                                       | X                 |                |                                                 |                                 |

\*Process evaluation will be conducted in intervention facilities only.

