- I. Facilities are eligible for the study if they 1) have at least 50 normal vaginal deliveries per month on average; 2) have at most 400 normal vaginal deliveries per month on average; 3) are owned by the government or a faith-based organization; 4) have no potentially confounding ongoing research or quality-improvement programs at the time of selection (especially mentorship or mHealth programs).
- II. Providers are eligible for the provider interview if they 1) are nurses or midwives; 2) provide maternity services; 3) have no plan to move to a different facility in the next 6 months (baseline only).
- III. Pregnant women presenting for antenatal visits are eligible for the study if they 1) are at least 15 years old; 2) have access to a mobile phone; and (3) are at least 16 weeks pregnant or in Month 5, 6, 7, 8, and 9 of pregnancy.  
Those under 18 years of age who are considered a mature minor will participate. Mature

minors are those who are married, a mother, pregnant, or a household head who are under 18 years of age.

- IV. Patients admitted for labor and delivery at participating facilities are eligible for the study if they 1) are at least 15 years old; 2) are admitted for labor and delivery at the maternity ward.

Pregnant women are excluded from the study if they 1) are presenting for conditions other than labor and delivery (e.g., patients admitted for prenatal observation or complications from abortion), 2) are immediately transferred to another hospital. We apply these exclusion criteria because of the study's focus on evaluating the intervention's impact on maternal and neonatal care in selected facilities.

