- 4) Enumerators will conduct two short follow-up interviews by phone. The first interview will occur towards the end of pregnancy and the second interview will occur at around 7- to 8-week postpartum. These interviews will contain questions about women's health care utilization, health knowledge, self-efficacy, health outcomes, and experience with the intervention (if applicable). Enumerators will confirm the identity of the participant before proceeding with the phone interviews. Participants who complete surveys will receive a small SMS credit. The phone interviews may be recorded for quality control purposes.

**Delivery observations:** medically trained enumerators will observe labor, delivery, and postpartum care and record information on quality of care during the endline period.

- 1) Enumerators, with the aid of the maternity in-charge, will decide in advance where to sit in different parts of the maternity ward so as to be able to observe the actions of the health workers, but be out of the way and non-disruptive.
- 2) Introduction and consent:
  - a. Upon arrival of a woman in labor, an enumerator will join the health staff in approaching and greeting the woman. Following the first examination and confirmation of admission, the enumerator will wait until an appropriate moment to begin consent procedures. The enumerator will not approach a woman for consent who is not stable or able to focus on the consent process. The enumerator will ask for the woman's consent before her first examination for her care to be observed and her records to be transcribed from the facility records (e.g., maternity register). The enumerator will not record information about the woman until consent has been given.
  - b. In some situations, a woman may be unable to give consent upon arrival to the facility but may later be sufficiently stable to give consent. In this situation, an enumerator may approach the woman once she is stable and able to give consent. As above, the enumerator will not record information about the woman until consent has been given.
- 3) Collecting clinical quality observation data:
  - a. If the woman consents to participate in the study, the enumerator will thank her and inform her that he/she and the other enumerators will not be giving any care to her during the duration of her delivery, but will only be present as observers.

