  - b. Enumerators will avoid speaking to patients or health workers, and will avoid sudden movements that may draw any attention.
  - c. The enumerator will follow the staff and woman to the maternity ward.
  - d. The enumerator will observe labor and delivery for as long as it is on-going, up until time of discharge from the facility, time when a patient is referred out and leaves the facility, or when a patient is going to receive a Cesarean section.
  - e. The enumerator may use the patient chart, partograph, the woman's antenatal care book, bill, or any other written notes or records to complete the observation tool. In cases when the antenatal care book is used, the enumerator will politely request for the book from the patient. The enumerator will only ask for the book at a time when it is not disruptive to other processes.
  - f. If the enumerator is satisfied with the checklist, all information will then be fed into the tablet. Information in the tablet must be identical to that on the paper form.
- 4) Protocol in case of emergencies:
  - a. Protocol for enumerators will be to not intervene in the care provided to the woman, unless in the case of a life-threatening emergency that could benefit directly from the enumerator's involvement. Should the enumerator observe gross mismanagement of a patient and he/she feels that the situation is life threatening, the enumerator may offer advice and/or assistance.
  - b. If an enumerator intervenes, they will do so in their capacity as a medical expert, not as a research observer. They must be medically qualified to intervene in the specific situation, that is, have had the necessary training to be qualified to provide care. If

possible, the enumerator should call the study team leader for advice on the way forward before intervening. All instances of enumerators offering assistance to health workers will be well documented. Enumerators should frequently but politely remind the health workers at the facility that they are only observers and not present to provide care or assistance.

**Process evaluation:** We will use program administrative data to assess the implementation of the intervention until study activities are complete in intervention facilities. This data is routinely collected by Jacaranda Health.

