**7.5. Will participants be offered a copy of the consent information?**  
☒ Yes ☐ No: *If no, explain why not.*

**7.6. If consent will be obtained in a language other than English, identify the language(s) that consent information will be provided, who will be responsible for translation, and the provisions for communicating this information to participants. ☐ N/A**

The patient consent forms will be written in English and translated into Swahili. The consent form will be read aloud by the field researcher in the language the patient prefers.

**7.7. If the research involves deception and/or incomplete disclosure, describe the debriefing process. Explain when participants will be debriefed, who will debrief them, and how they will be debriefed. ☒ N/A**

**7.8. If the research involves secondary use of existing data, documents, records, and/or specimens, and the research team will not obtain consent, describe how consent was originally obtained. Additionally, either upload the original consent form to the ESTR record or confirm that the original consent process obtained participants’ permission to share or use their data/specimens for future research projects. ☐ N/A**

We will collect data from existing medical records kept at health facilities (e.g., the MOH333 Maternity Register). Enumerators will enter the register data into tablets without any personally identifying information (i.e., name, date of birth, or contact information) and we will not obtain consent. In the endline, for the patients who consent to being observed, enumerators will also obtain patients’ consent to access their medical records in health facilities. For this subset of patients, we will collect data from their health records with identifying information.

We will extract administrative data that Jacaranda Health routinely collects on the implementation of the interventions. We will only extract individually identifiable data from program records for participants that have consented to the study. This will allow us to link data on intervention use with the survey data we collect. For program records without individual consent, we will only collect aggregated data.

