**16.2. Is there a sample size/power calculation?**

☐ No ☒ Yes: *If yes, describe the calculation and the scientific rationale, and, if applicable, by site and key characteristics such as participant demographics.*

The baseline sample size is based on the power calculation for postnatal care within 6 weeks of delivery, which is our primary outcome for patient care seeking. Based on Jacaranda's internal data, we assume that 61% of women will receive any postnatal care visit within 6-8 weeks of delivery in the absence of the intervention. Based on health information system volume data, we would expect to see 120 ANC patients new to the intervention in study facilities in a given month and we expect at least 80% of them will be enrolled into the PROMPTS intervention. We plan to enroll women over at least a one-month period to reach this target. Assuming that we can track 75% of these women postpartum regarding post-delivery outcomes, we would expect to follow roughly 58 women for this outcome in each facility. Assuming an ICC of 0.01, the minimum detectable impact is an increase in postnatal care receipt of 7 percentage points or a 11% increase in postnatal care seeking.

The endline sample size is based on the power calculation for quality of care during labor, delivery and immediate postpartum, which is our primary health worker outcome. We assume that we will be able to observe at least 100 complete deliveries during six weeks of observation in each facility at the endline. Based on the PIs recent work in Uganda and Kenya, which used a very similar technique of clinical observations of deliveries in similar health facilities, we assume that average quality of care for the control group will be 0.58 (i.e., health workers will perform just over half of the important aspects of quality of care) with a standard deviation of 0.13. Assuming an intra-cluster correlation (ICC) of 0.35 (based on baseline data from our previous work), a cluster size of 100 patients, 20 clusters per arm, alpha of 0.05, and power of 0.80, the minimum detectable impact would be 6.88 percentage point increase in quality of care or an 11.9% increase in the quality-of-care index.

**17. Costs and Compensation** ☐ N/A. *Skip to next section.*

**17.1. Identify any costs that participants may incur during the study, including transportation costs, childcare, or other out-of-pocket expenses.**

There are no other anticipated costs that participants may incur during the study.

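### The sample size counts antenatal patients new to PROMPTS, but eligibility does not screen out current users, and the protocol does not commit to measuring PROMPTS exposure in control women

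*Protocol*

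**What the plan says.** **Sample size (section 16.2).** For postnatal care the text states that "we would expect to see 120 ANC patients new to the intervention in study facilities in a given month". It expects at least 80% of them to enrol in PROMPTS and 75% to be tracked postpartum. It arrives at about 58 women followed per facility and a minimum detectable increase of 7 percentage points on a 61% control rate.

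**Eligibility of women (section 5.5).** The rule opens "Pregnant women presenting for antenatal visits are eligible for the study if they 1) are at least 15 years old". The remaining conditions concern phone access and gestation (at least 16 weeks, or month 5 to 9). It does not mention current or past PROMPTS enrolment.

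**Sources of exposure data.**

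- Section 5.1, table footnote: "Process evaluation will be conducted in intervention facilities only".
- Section 5.7, on the same activity: "We will use program administrative data to assess the implementation of the intervention until study activities are complete in intervention facilities".
- Section 5.7, topics of the follow-up phone interviews: "health outcomes, and experience with the intervention (if applicable". The text does not say which women this applies to.
- Section 7.8: "We will only extract individually identifiable data from program records for participants that have consented to the study". The stated purpose is: "This will allow us to link data on intervention use with the survey data we collect". Consent is the condition, and trial arm is not mentioned.

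**Safeguards.** Section 5.5 excludes facilities with a potentially confounding mentorship or mHealth program at selection. Section 5.1 requires enough distance between the facilities in the sample, without giving a minimum.

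**The concern.** The women counted for power and the women who may be enrolled are defined differently. PROMPTS runs on a woman's own phone, so she keeps it when she changes clinic. Because recruitment extends to month 9, a woman may have signed up at an earlier visit elsewhere and then join the trial at a control facility.

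Two things are at stake. First, each exposed control woman pulls the as-randomised difference in postnatal care towards zero. Second, unless exposure is ascertained in controls, a small or null result cannot be separated from dilution. Prior enrolment is also a matter of timing: it can be screened for only at recruitment. Eligibility and data collection are fixed in the protocol, so this is not a detail that can wait for an analysis plan.

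**Working it through.** **Step 1. Set the sections side by side.**

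| Question | Where | Answer |
|---|---|---|
| Who is counted for power? | 16.2 | Antenatal patients new to the intervention |
| Who may be enrolled? | 5.5 | Any attendee meeting the age, phone and gestation criteria |
| Where is process evaluation done? | 5.1, 5.7 | Intervention facilities only |
| Whose program records may be linked? | 7.8 | Any consented participant, with no limit by arm |
| Who is asked about experience with PROMPTS? | 5.7 | Those to whom it applies, not defined |

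The first two rows do not match. The last three permit exposure measurement in controls but do not require it.

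**Step 2. Reproduce the stated detectable difference.** Inputs from section 16.2 are a 61% control rate, 58 women per facility and an ICC of 0.01. The figures of 20 facilities per arm, alpha 0.05 and power 0.80 are given there for the quality-of-care outcome. I assume they apply here too, with a two-sided test.

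- Design effect: 1 + (58 − 1) × 0.01 = 1.57
- Effective number per arm: 20 × 58 / 1.57 = 738.9
- Two-proportion normal approximation, solved for 80% power: 6.97 points
- Relative increase: 7 / 61 = 11.5%

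This agrees with the stated 7 points. None of the inputs allows for exposed controls.

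**Step 3. Illustrate dilution.** Let *c* be the share of control women exposed. Suppose each gains the full 7 points. The control rate becomes 61 + 7*c* against 68 in the intervention arm, so the difference is 7 × (1 − *c*). The effect needed to keep about 80% power is the undiluted detectable difference (6.96 points with unpooled variance) divided by (1 − *c*).

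| Assumed *c* | Difference, points | Power | Undiluted effect needed for about 80% power, points |
|---|---|---|---|
| 0 | 7.00 | 80.3% | 7.0 |
| 5% | 6.65 | 76.3% | 7.3 |
| 10% | 6.30 | 71.8% | 7.7 |
| 20% | 5.60 | 61.8% | 8.7 |

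For the 10% row, the standard error is 0.02484 under the null and 0.02479 under the alternative. Then (0.063 − 1.96 × 0.02484) / 0.02479 = 0.577, which gives power of 0.718.

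**Step 4. Sensitivity to cluster size.** The stated factors give 120 × 0.80 × 0.75 = 72 women per facility, not 58, which is a separate matter. With 72, power at *c* = 0, 5%, 10% and 20% is 85.2%, 81.5%, 77.3% and 67.5%. The level is higher and the pattern is the same.

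**The case against.** Four points can be made for the protocol.

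1. **Linkage is already allowed.** Section 7.8 makes consent the condition, control women in the antenatal cohort are consented, and their contact details are held. This stands. A reader might infer from the footnote that no planned source could reveal control exposure. The documents do not support that: the footnote limits the process evaluation, not every measurement of exposure. The follow-up item in section 5.7 can also be read as covering any woman who received the service, in either arm, and the questionnaires are not shown.

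2. **There are safeguards against contamination.** The facility-level mHealth exclusion and the distance rule lower the risk. They act on facilities, however. The distance rule concerns only facilities in the sample, and neither rule stops an individual woman who enrolled elsewhere.

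3. **The sample-size wording may be only a volume estimate.** It might separate newly enrollable women from repeat visits. A reader might infer that the sponsor expects a material share of attendees to be exposed already, but the text does not say so. The mismatch with section 5.5 remains on either reading, because eligibility does not ask for newness.

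4. **The power loss is assumed.** This also stands. A reader might infer a steeper loss by treating the 7 points as produced wholly by PROMPTS at 80% uptake, so that the effect is 7 × (0.80 − *c*) / 0.80. That gives 6.6, 6.1 and 5.3 points at 5%, 10% and 20%. The documents do not support it. The trial tests a package, and control women cannot carry MENTORS with them on a phone. Section 16.2 also applies the 80% before reaching its 58 women, so dividing by it again may count uptake twice.

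**Conclusion.** The point holds as an internal mismatch and a missing commitment. Followed as written, section 5.5 admits women already on PROMPTS although section 16.2 counts new ones. Sections 5.1 and 5.7 confine the process evaluation to intervention facilities, while section 7.8 leaves control-arm linkage open without requiring it. Control uptake could therefore go unascertained.

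The direction of the effect is clear: control exposure dilutes the as-randomised difference. Its size cannot be derived from the documents. The fall in power from about 80% to 76%, 72% or 62% is an illustration. It rests on an assumed 5% to 20% exposure, on exposed controls gaining the full 7 points, and on 20 facilities per arm applying to postnatal care. Because the 7 points belong to the package, PROMPTS alone may carry less than that, and the dilution would then be milder. The correction is worth making because it is cheap now and prior enrolment cannot be screened for later.

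**What to change.** 1. **Section 5.5:** ask every antenatal candidate in both arms, at baseline and before PROMPTS is offered, whether she is currently enrolled in PROMPTS. Make not being enrolled an eligibility criterion in both arms, so that the enrolled population matches section 16.2.
2. **Sections 7.8 and 5.7:** state that program-record linkage and the follow-up question on exposure cover consented women in both arms. Screening alone would not catch control women who enrol later.
3. **Section 5.1, footnote:** amend it so that ascertaining PROMPTS enrolment is an exception to the restriction to intervention facilities.
4. **Reporting:** present PROMPTS uptake by arm beside the as-randomised result.

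The cost is one extra question, one match against records the program already holds, and consent wording for control women. Some already enrolled women would be lost, probably few given the facility-level mHealth exclusion. Their exclusion narrows the population slightly, which the sponsor should accept explicitly.

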## 5.2. Does the study involve more than one participant group?

☐ No ☒ Yes: If yes, identify each group here and throughout all applicable sections.

- I. Facility and maternity in-charges, pharmacists, phlebotomists, and other health workers that are familiar with the operations at different departments at selected health facilities
- II. Nurses, midwives, and other health workers working in the maternity wards at the selected health facilities
- III. Women visiting health facilities for antenatal care
- IV. Women admitted to health facilities for labor and delivery

## 5.3. Indicate the total duration of a participant's involvement.

- I. In-charges and other providers at health facilities will be engaged for approximately 2-3 days during the baseline data collection period for the facility assessment.

- II. Nurses, midwives, and other health workers in the maternity wards will be engaged on an ongoing basis during the endline survey over a period of 1-2 months for delivery observations. Nurses and midwives will also be engaged for the provider survey, which will last about 1 hour during both baseline and endline data collection periods.
- III. Women visiting health facilities for antenatal care will be engaged for about 10-15 minutes to complete a survey. They will be contacted by phone for the two follow-up surveys. These phone surveys will last for about 15-20 minutes. In addition to the phone calls for data collection, there is a small chance that participants will receive a follow-up call for data quality assurance.
- IV. Women admitted to selected health facilities for labor and delivery will be engaged from arrival/admission to facility to end of discharge from facility in the endline data collection periods.

**5.4. Indicate the total number of participants to be screened (if applicable) and/or enrolled (i.e., signed consent form). If the proposed research involves secondary data analyses only, indicate the number of data, documents, records, and/or specimens that will be obtained.**

- We plan to enroll about 40 facilities for the facility assessment.
- We plan to enroll about 200 nurses and midwives (about 5 per facility) from study facilities for the provider survey.
- We plan to enroll about 4800 women (about 120 per facility) who are seeking antenatal care in study facilities.
- We plan to enroll about 4800 women admitted for labor and delivery (about 120 per facility) for delivery observations.
- We plan to collect register data for the time period that covers 12 months prior to the baseline and up to 12 months after the endline.

**5.5. List inclusion and exclusion criteria and describe the screening process. Provide a rationale for any specific exclusion criteria.**

- I. Facilities are eligible for the study if they 1) have at least 50 normal vaginal deliveries per month on average; 2) have at most 400 normal vaginal deliveries per month on average; 3) are owned by the government or a faith-based organization; 4) have no potentially confounding ongoing research or quality-improvement programs at the time of selection (especially mentorship or mHealth programs).
- II. Providers are eligible for the provider interview if they 1) are nurses or midwives; 2) provide maternity services; 3) have no plan to move to a different facility in the next 6 months (baseline only).
- III. Pregnant women presenting for antenatal visits are eligible for the study if they 1) are at least 15 years old; 2) have access to a mobile phone; and (3) are at least 16 weeks pregnant or in Month 5, 6, 7, 8, and 9 of pregnancy.  
Those under 18 years of age who are considered a mature minor will participate. Mature

minors are those who are married, a mother, pregnant, or a household head who are under 18 years of age.

- IV. Patients admitted for labor and delivery at participating facilities are eligible for the study if they 1) are at least 15 years old; 2) are admitted for labor and delivery at the maternity ward.

Pregnant women are excluded from the study if they 1) are presenting for conditions other than labor and delivery (e.g., patients admitted for prenatal observation or complications from abortion), 2) are immediately transferred to another hospital. We apply these exclusion criteria because of the study's focus on evaluating the intervention's impact on maternal and neonatal care in selected facilities.

